**Randomization**

Participants meeting the inclusion and exclusion criteria will be approached, screened, consented, and enrolled into the study. After obtaining informed consent, participants will be randomized to either the experimental (RGT) or UC control group using cluster randomization based on specific injury characteristic for stratified block.

The heterogeneity of the population in terms of injury severity is a concern given that these factors are expected to be important to walking recovery. To account for this, patients will be assigned to RGT or UC using 1:1 stratified blocks. Stratification will be based on specific injury characteristics (incomplete tetraplegia and incomplete paraplegia), and within each strata randomization blocks of size 6 will be used to ensure equal distribution between groups.

[figure not shown]

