# **9 STATISTICAL METHODS**

**Sample Size Considerations**

For the proposed project, 128 patients (64 per group) will be enrolled. All analysis will be performed using SAS 9.4 significance set at the 5% level. Sample size calculations were performed to determine the required sample size in each group based on detectable effect size. For 80% power with a 5% significance level we will need to obtain 64 participants in each group to detect a medium effect size of 0.5 and allow for ~10% attrition due to unplanned medical events, acute care transfers, and patient withdrawals. We anticipate minimal attrition as all treatments and outcomes will be assessed during the inpatient rehabilitation stay and we experienced 0% attrition during our feasibility study.

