Hypothesis 3.1: *RGT will be of significantly greater intensity with participants (1) spending more minutes per session and total minutes (over all sessions) in moderate intensity exercise (40% to 60% range of heart rate reserve), (2) reporting higher mean RPE across all sessions, and (3) completing more steps during each session and total number of steps over all sessions compared to UC.*

Hypothesis 3.2: *Intensity will be significantly correlated to the primary outcome (WISCI-II) for the RGT and UC groups.*

Hypothesis 3.1 will be evaluated using similar methods as Aim 2. Moderate intensity minutes, average RPE, and steps will be evaluated using individual general or generalized linear models, as appropriate, to determine the association between RGT and UC and intensity. Each model will control for the patient characteristics listed in section B.1.i.D and total number of sessions. Additionally, to determine the relationship between session intensity and walking function (Hypothesis 3.2) correlation coefficients will be calculated between each intensity measure and WISCI-II at admission, discharge, and change score.

For both Aims 2 and 3 stratified subset analysis will be performed for tetraplegia and paraplegia to determine if RGT has a differing impact depending on injury classification.

**Missing Data:** If a patient misses an assessment, their data for that outcome will be treated as missing and *will not* be included in the statistical model. However, the data from the completed assessments for that patient *will* be included. Sensitivity analysis will be performed to assess the impact of missing data, by imputing a missing outcome measure using the overall average change score for the given outcome. The sensitivity analyses will be compared to the initial analysis to determine the impact of missingness on the results

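### The protocol's only named missing-data check will usually repeat the complete-case test result and cannot detect bias from outcome-related dropout

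*Protocol*

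**What the plan says.** Under Missing Data (section 9, Study Analysis Methods), a missed assessment is treated as missing and omitted from the model for that outcome, so the primary analysis is complete-case. One sensitivity analysis follows, "by imputing a missing outcome measure using the overall average change score for the given outcome". Its results are to be set against the initial analysis to judge the effect of missingness. The section gives no imputation variance, no arm-specific imputation and no scenario in which lost patients do worse.

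The Aim 2 Analysis uses general or generalized linear models adjusted for admission score and patient characteristics. Sample Size Considerations plans 64 per group "to detect a medium effect size of 0.5" and expects about 10% "attrition due to unplanned medical events, acute care transfers, and patient withdrawals". It adds that "we experienced 0% attrition during our feasibility study".

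**The concern.** The named causes of loss (medical events, acute transfers, withdrawal) could plausibly go with poorer recovery. The check gives such patients average recovery, gives it equally to both arms, and treats the filled values as observed data. Equal filling pulls the difference towards zero. Treating filled values as observed shrinks the standard error. If the two effects nearly cancel, the check will tend to agree with the primary test whether or not that test is biased. A reader would then take the agreement as evidence that missing data did no harm.

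**Working it through.** **Inputs from the protocol.** 64 per arm, 1:1 allocation, effect 0.5 SD, 5% significance (taken as two-sided), about 10% loss not split by arm. The protocol gives no admission-to-discharge correlation, residual SD or loss mechanism. Those below are assumptions.

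**The protocol's own figure.** n per arm = 2(1.96 + 0.84)²/0.5² ≈ 63, and the t-test gives 63.8, so 64 (power 0.801). This reproduces with no loss. The protocol states no figure for the missing-data check itself.

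**Algebra for a change-score contrast.** Let retention be a and b in the two arms. The pooled mean change is (a·x₁ + b·x₂)/(a + b). After filling:
- effect multiplier = 2ab/(a + b)
- naive SE multiplier ≈ √(ab)
- t multiplier ≈ √(ab)/((a + b)/2), which is 1 when a = b

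| Loss by arm | Effect | SE | t |
|---|---|---|---|
| 10% / 10% | ×0.90 | ×0.90 | ×1.00 |
| 20% / 20% | ×0.80 | ×0.80 | ×1.00 |
| 20% / 0% | ×0.889 | ×0.894 | ×0.994 |

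**Admission-adjusted model, random loss.** Take total SD 1 and correlation 0.6, so residual SD = √(1 − 0.36) = 0.8. With full data SE = 0.8·√(2/64) = 0.141. With 10% loss it is 0.8·√(2/57.6) = 0.149. In simulation the imputed analysis moves the estimate from 0.50 to about 0.45 and the SE from 0.149 to 0.137, which is smaller than if nobody had been lost. Mean z is about 3.3 in both. Agreement on significance at 10% random loss:
- d = 0.5, correlation 0.6 (power about 91%): 98%
- d = 0.4, correlation 0.6 (power about 75%): 96%
- d = 0.5, correlation 0.3 (power about 79%): 94%

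Coverage of the true effect by the imputed interval is about 93–94% at 10% loss and 88–90% at 20%.

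**Outcome-related loss, no true effect.** Assume 15% of RGT and 5% of UC are lost, and that lost patients do 1.5 SD worse. If the effect among patients who stay is c, the as-randomised effect is c − 0.15×1.5 + 0.05×1.5 = c − 0.15. It is zero when c = 0.15.
- Complete-case: z is centred at 0.15/0.149 ≈ 1.0, so rejection is about P(|Z + 1.0| > 1.96) ≈ 17%.
- Imputed: the effect multiplier is 2(0.85)(0.95)/1.80 = 0.897, so the effect is 0.135. With SE about 0.137, z ≈ 0.98 and rejection is about 16%.
- Simulation gives about 17% for both analyses, against about 5% with full data.

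A second mechanism (no true effect, 40% of below-average responders lost from RGT only, residual SD 1, admission slope 0.7, 4,000 trials) gives 18.6% complete-case and 18.1% imputed, against about 5% with full data.

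**Loss related to admission score, RGT only.** Assume d = 0.5, residual SD 1, and 40% of the lower half by admission score lost from RGT (10% overall).

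| Admission slope | Complete-case estimate | Imputed estimate | Rejection, complete-case v imputed | Agreement |
|---|---|---|---|---|
| 0.5 | 0.50 | 0.36 | 74.6% v 54.0% | 79% |
| 0.2 | 0.50 | 0.31 | 74.3% v 40.0% | 66% |

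Here the complete-case model is unbiased and the imputation creates the discrepancy.

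**The case against.** A reader might infer that the check reproduces the primary result by construction. The documents do not support that. The near-exact cancellation belongs to a change-score contrast with similar loss in both arms, whereas the Aim 2 models adjust for admission score. There agreement is approximate, and the last table shows it can break.

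Four further points count against the concern.
- **Attrition may be low.** The feasibility study had none and all assessments fall within the inpatient stay. The protocol still plans to "allow for ~10% attrition due to unplanned medical events, acute care transfers, and patient withdrawals", and the null scenarios above lose only about 10% overall.
- **The interval harm is modest.** At the planned loss, coverage falls by one or two percentage points. The larger shortfall needs 20% loss.
- **The comparison is not limited to significance.** A reader comparing estimates would see a shift of about 10%. That shift is mechanical and says nothing about bias. It moves towards the truth when complete-case overstates the effect. With the losses reversed (5% RGT, 15% UC) and c = 0.5, the true effect is 0.5 − 0.075 + 0.225 = 0.65, and the estimate moves away from it, from 0.50 to 0.897×0.50 = 0.45.
- **A SAP may say more.** It may, and details absent here are no fault. The criticism is of the method the protocol does state for a purpose it also states.

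The word *overall* could instead mean each arm's own average. The effect would then stay put while the SE shrank by about (1 − m), where m is the fraction lost, inflating t by 1/0.9 ≈ 1.11 at 10% loss. That is a different fault and no defence.

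**Conclusion.** The concern holds in a limited form. The stated check will usually repeat the complete-case test result (about 94–98% of simulated trials at 10% random loss) and cannot reveal bias from outcome-related dropout. Under the assumed 15% v 5% loss it repeats a false-positive rate of about 17%. It can also signal trouble where there is none, when loss depends on admission score in one arm. Undercoverage is a minor matter at 10% loss.

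These sizes rest on assumed correlations, residual SDs and loss mechanisms, and on reading *overall* as pooled over arms. Nothing here shows that the primary estimate will be biased. The fault lies in the check and in the reassurance drawn from it, and it should be corrected.

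**What to change.** In the Missing Data paragraph, replace the average-change imputation with multiple imputation done separately by arm, using admission score and injury stratum (tetraplegia or paraplegia), combined by Rubin's rules. Add the ASIA Impairment Scale only where it is recorded: section 6 describes it for severity after traumatic SCI, while Table 4 also admits non-traumatic injury.

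Multiple imputation of this kind handles loss related to admission score but still assumes that lost patients resemble similar patients who stayed. So add a delta-adjusted (tipping-point) analysis: worsen the imputed outcomes of lost patients progressively, with the shift allowed to differ by arm, and report the delta at which the conclusion changes.

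Fix both before outcomes are examined by arm. The cost is a few hours of programming with standard procedures in the SAS already planned. Data collection and the primary analysis stay as they are.

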# **11 INVESTIGATOR’S RESPONSIBILITIES**

**Investigator Responsibility**

The principal investigator will be responsible for the conduct of all study activities and safety of participants, including maintaining confidentiality for participants. The principal investigator will also maintain a staff delegation of authority list of appropriately qualified persons to whom the principal investigator has delegated study-related duties. All activities will be performed in accordance with BSWRI policy and federal guidelines.

# **12 ETHICS**

**Institutional Review Board**

The protocol will be reviewed by the Baylor Scott & White Research Institute Institutional Review Board. No study procedures will begin until the principal investigator receives written IRB approval for the protocol, informed consent, and other study documents. The principal investigator will submit continuing review reports on the status of the study. All revisions and events will be reported to the IRB as per federal regulations.

**Ethical Conduct of the Study**

Baylor Scott and White Research Institute has established human subject protection committees that will review and approve all study protocols, informed consent, and documents related to this study. All investigators listed on the project are certified as having completed the Collaborative Institutional Training Initiative human subject protection training and affiliated their credentials with Baylor Scott and White Research Institute. Only study personnel will have access to any personal information. The data collected will not be used to identify individuals and no personally identifiable data will be used in any format (e.g., analysis, presentation, publication, discussion). All participants will be given unique subject IDs and the decoding matrix will be stored on a password-protected Excel spreadsheet on a Baylor computer and will only be available to the principal investigator and delegated study staff. Subject IDs will be used for analysis. Participants will be made aware of efforts to protect their confidentiality.

**Risks and Benefits**

*Physical risks***:** Participants may experience orthostatic hypotension, skin breakdown, falls, fracture, overheating, and autonomic dysreflexia if they have difficulty due to impaired motor and sensory function common to SCI population. All therapy staff is trained to observe and monitor for these risks and methods to limit or resolve these potential concerns.

*Psychological risks***:** Participants may experience frustration during RGT due to motor and sensory deficits common to SCI population. All staff is trained to observe and monitor for frustration and methods to limit or resolve these potential concerns (i.e. institute rest breaks, maintain supervision).

*Social risks***:** No social risks have been identified by participating in this study.

*Legal risks***:** No legal risks have been identified by participating in this study.

*Economic risks*: No economic risks have been identified by participating in this study.

*Direct benefit to research participants*

See below for potential future benefits.

*Potential future benefits to individuals with the condition being studied*

The benefits to participants may include gaining greater walking function and improved health. Study findings could help rehabilitation clinicians identify evidence-based practice walking interventions and facilitate best practice guidelines for patients with SCI.

*Potential benefits to society in general*

The information gained in this study will help validate the importance and benefits of exoskeleton gait training in the outpatient rehabilitation setting for spinal cord injury patients.

*Potential benefits to others involved in research*

Clinicians involved in this research will contribute to evidence-based practice research methods, and facilitation of improvements for best practice for spinal cord injury patients.

*Risk to benefit analysis*

The risks posed to study subjects (e.g. injury while engaging in physical activity, psychological stress associated with treatment) are minimal, while the study poses benefits to the study participants in terms of improved walking recovery after SCI and overall health and function. The research poses potentially great benefits to society, as individuals with SCI and rehabilitation clinicians desire enhanced walking recovery to allow greater independence with mobility for activities and community participation.

It is hoped that the information gained from this proposed study will contribute to an evidence base for a walking retraining intervention with input from key stakeholders that integrates known critical ingredients and established principles of neuroplasticity to specifically address the unique needs of people with incomplete SCI.

# **13 STUDY DOCUMENTATION AND RECORDKEEPING**

In order to assure participant confidentiality, all participants will be assigned a unique study identification number. Only one master list will be maintained by the PI and the study coordinator on a secure network drive in a password protected file. All case report forms and databases will use the subject ID number rather than names or other private health information. Signed consent forms and case report forms will be maintained by the PI behind a locked door in a locked file cabinet.

**Documentation of Data**

All participants will be given a subject identification number. This number will be used on all data collection forms and databases to ensure patient confidentiality. Hospital dates, onset of injury and demographic data will be extracted from patient report or medical record. Other data points can be collected from the participant directly onto the data collection form by the treating clinicians (or a member of the research team). Non-electronic data will be stored in a secured cabinet in the Research Office Suite. Data will then be entered into a secure database that only the study team will be able to access.

**Data Collection and Data Entry into Database**

Research material obtained from study participants will be collected from medical records and assessment and intervention data. All materials will be obtained specifically for research purposes. Members of the research team will collect demographic, physiologic, quantitative observational and/or qualitative information from participants during the study. Demographic, observational and qualitative data will be collected during Aim 2 at admission and discharge inpatient rehabilitation time points at BSW and entered into a secure SAS database by research staff. Physiologic data will be collected during Aim 3 throughout the intervention at BSW. Qualitative/survey data obtained during the admission and discharge time points will be entered into our secure BSW server. All demographic, observational, and physiologic data will be recorded on paper source documents and later entered to either REDCap or SAS database by research staff. All data will be stored on a secure server, with security meeting BSWRI standards.

Data will be collected via our medical record (Epic), patient interviews, and testing conducted by the study coordinators. Patient testing for study specific patient-reported outcomes will be conducted in the research lab, located in the inpatient rehabilitation hospital. We anticipate study specific assessments to require 1 hour/assessment. Clinical measures and measures of intervention intensity (e.g., HR, RPE) will be assessed by the treating physical therapists during therapy sessions as part of usual care. The outcome assessment schedule is depicted in **Table 7**.

The following data will be collected through the medical record and patient interview: age; age at injury; injury severity; gender; ethnicity; education level; pre-morbid history of mental illness; residence status; income; insurance type; vocation; and financial status. Level of impairment will be captured using the ASIA Impairment Scale (AIS) to determine injury severity after traumatic SCI by the physician at admission to BSW. The AIS is standard of care at BSW and will be extracted from the medical record.

**Record Retention**

All paper source documents will be kept in a double locked storage cabinet in the BSWIR research office. All electronic data will be kept on a secure server per federal guidelines. All data will be maintained for two years after study termination per federal guidelines and will be disposed of in accordance to current BSWRI policy.

**Protocol Deviations**

All protocol deviations will be recorded in the participant’s chart and regulatory binder as they occur, and subsequently formally to the IRB at continuing review

**Management of Subject Safety/ Adverse events**

The study staff (PI, Co-Investigators, research coordinators and assistants) will be responsible for collecting and recording all clinical data. As results are collected, all Adverse Events will be identified, graded for severity and assigned causality. **Only those adverse events directly related or caused by the study will be reported to the IRB and compiled for periodic review**. After assigning causality, the PI will decide the course of action for the study participant. The PI will evaluate all Adverse Events and determine whether the Adverse Event affects the risk/benefit ratio of the study and whether modifications to the protocol or informed consent form are required*.* Throughout this process, the PI will inform and collaborate with the research team.

The plan to monitor participant data and safety will specifically include the following: (1) [name] (PI) will inspect collected data; (2) The IRB offices will be contacted if there is an Adverse Event due to participation; (3) the research protocol will be revised if it is determined that the protocol or intervention presents an unforeseen risk to participants; (4) if an event occurs that requires immediate attention and [name] is unavailable, then members of the research team will follow the emergency procedures put in place by the research team, which may include calling emergency medical services.

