UC gait training at BSWIR adheres to the current SCI-specific clinical practice rehabilitation guidelines. These guidelines recommend that body weight–supported treadmill training (BWSTT) as an option for ambulation training in addition to conventional overground walking, dependent on resource availability, context, and local expertise.^65^ BSWIR currently offers 2 BSWTT systems, 1 overground body weight-supported overground system, and various assistive devices (e.g., walkers, leg braces) to perform manually assisted overground gait training. BSW therapists are trained and proficient in providing UC gait training interventions to patients with SCI. Patients in the UC group will receive 90 minutes per week of UC gait training (e.g., BWSTT, overground with braces).

If participants are randomized into the usual care group and have completed care, they will be offered up to eight optional sessions of robotic walking training in outpatient therapy at BSWIR in Dallas, Texas. Participants will need to obtain a physician referral and arrange their own transportation.

*RGT*

Patients in the RGT group will receive 90 minutes per week of RGT in the Ekso device once patients are deemed clinically appropriate as defined by being able to tolerate standing for 15 minutes without orthostatic intolerance. The Ekso Bionics Ekso GT™ robotic exoskeleton will be used for RGT.

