**Data Safety and Monitoring Board**

A 3-member external Data Safety and Monitoring Board (DSMB), including a Chairperson, will be established for FIRST. The DSMB will monitor the study and review quarterly the following: a) participant recruitment, accrual, retention, and withdrawal information; b) adverse events (AEs) and serious adverse events (SAEs); c) comparison of events that occur between treatment arms; d) individual events of particular concern; e) participant interview and/or performance status outcomes; f) other safety-supporting data requested by the DSMB; and g) summary of protocol violations, completeness and timeliness of study visit data, enrollment eligibility and ineligibility information, noncompliance, and unanticipated problems. None of these individuals on the DSMB will be directly involved in conducting this project or have a stake in its outcome. Funding for the DSMB is included in the budget and includes $300 per member, per year. Each DSMB member will meet at the beginning of the study with the PI and Co-Investigators to learn about the aims of the project, study design, and intervention.

The biostatistician will provide a data report four weeks prior to the DSMB teleconference meeting. Based on these Quarterly reviews, the DSMB may request specific responses from the PI. For example, the PI may be asked to provide additional plans for safety after a severe AE. The DSMB annual reports will enumerate the dates that the Committee meets, and its explicit procedures for monitoring patients’ safety and confidentiality, and data integrity, during the reporting interval. Actions taken by the IRB in response to AE reports will be immediately reported to the Project Officer and Research office.

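### The adverse-event section compiles only study-related events for periodic review, while the DSMB section promises a between-arm comparison of events with no such limit; the two must be reconciled

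*Protocol*

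**What the plan says.** **Section 13, Management of Subject Safety/Adverse events.** Capture is complete: "all Adverse Events will be identified, graded for severity and assigned causality". The principal investigator then looks at every event: "The PI will evaluate all Adverse Events and determine whether the Adverse Event affects the risk/benefit ratio of the study". Compilation is filtered, in a sentence set in bold: "Only those adverse events directly related or caused by the study will be reported to the IRB and compiled for periodic review".

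**Section 8, Data Safety and Monitoring Board.** "The DSMB will monitor the study and review quarterly the following", and the list that follows includes "b) adverse events (AEs) and serious adverse events (SAEs); c) comparison of events that occur between treatment arms". No relatedness condition is attached to either item. On the source of the data the section says only: "The biostatistician will provide a data report four weeks prior to the DSMB teleconference meeting". Which adverse events that report contains is not stated.

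**Section 4, Study Treatment.** The control arm is the site's normal practice: "UC gait training at BSWIR adheres to the current SCI-specific clinical practice rehabilitation guidelines". It is set at 90 minutes a week, the same amount as RGT.

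**The concern.** The two sections describe different sets of events. Section 8 needs all events, by arm. Section 13 is the only place that says what is compiled, and it keeps only events attributed to the study. A team that follows Section 13 literally could hand the DSMB a table that cannot support the comparison in Section 8.

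Randomisation makes an all-cause comparison fair: both arms share the same background of injury-related events, so an excess in one arm is informative without anyone judging causes. Filtering on attribution puts staff opinion in place of that comparison. The protocol describes no masking of treatment, and the staff delivering exoskeleton or usual-care training cannot be unaware of the arm. The physical risks listed in Section 12 (orthostatic hypotension, skin breakdown, falls, fracture, overheating, autonomic dysreflexia) are tied there to impairments common after spinal cord injury, so they can arise in either arm. For such events the cause in an individual patient is hardest to judge and the arm comparison is most useful.

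**Working it through.** **1. The passages side by side**

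| Question | Section 8 (DSMB) | Section 13 (adverse events) |
|---|---|---|
| Which events? | Adverse and serious adverse events, no limit | Only those directly related to or caused by the study |
| For whom? | DSMB | IRB, and a periodic review whose owner is not named |
| How often? | Quarterly | Not stated |
| By arm? | Yes | Not stated |
| Unrelated events? | Included by the plain wording | Identified, graded and evaluated by the principal investigator, but not compiled |

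No other section provides for tabulating unrelated events by arm.

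**2. What the filter does to a comparison**

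There is no figure in the protocol to reproduce. Let p be the true proportion of patients with an event, s the share of events judged related, and n = 64 per arm (Section 9). Counting one event per patient, the expected compiled count in an arm is n × p × s. The compiled ratio of RGT to usual care (UC) is therefore the true ratio multiplied by s(RGT)/s(UC), and the compiled excess is n × [p(RGT) × s(RGT) − p(UC) × s(UC)]. Unless s is 1 in both arms, the table mixes event rates with attribution habits.

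**3. Illustration (every p and s is an assumption)**

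The last column is the chance that a two-sided Fisher test gives p < 0.05. It is the sum over all pairs of counts (x, y) with Fisher p < 0.05 of Bin(x; 64, p(RGT) × s(RGT)) × Bin(y; 64, p(UC) × s(UC)). The protocol prescribes no such test; it serves only as a yardstick.

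| True rate, RGT v UC | Share judged related, RGT v UC | Expected compiled, RGT v UC | Chance of p < 0.05 |
|---|---|---|---|
| 20% v 20% | all compiled | 12.8 v 12.8 | 3% |
| 20% v 20% | 50% v 5% | 6.4 v 0.6 | 45% |
| 20% v 20% | 50% v 0% | 6.4 v 0 | 63% |
| 30% v 10% | all compiled | 19.2 v 6.4 | 77% |
| 30% v 10% | 30% v 10% | 5.8 v 0.6 | 35% |

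Example of the count: 64 × 0.20 × 0.50 = 6.4 and 64 × 0.20 × 0.05 = 0.64.

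With equal true rates and a UC share between 0 and 10%, the compiled counts run from 1.9 v 0–0.6 (10% true rate, 30% of RGT events judged related) to 15.4 v 0–1.9 (30% true rate, 80% judged related).

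Rows 2 and 3 show a false signal against RGT. Row 5 shows a real excess partly hidden: the expected excess falls from 19.2 − 6.4 = 12.8 patients to 5.76 − 0.64 = 5.1.

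**The case against.** The strongest reply is that Section 13 never mentions the DSMB. The oversight body in that sentence is the IRB, and Section 12 and the Protocol Deviations paragraph of Section 13 both refer to continuing review by the IRB. If that is the periodic review meant, the filter governs IRB business, Section 8 stands alone with its unrestricted remit, and the DSMB can also request further safety data. This reading is open. It does not settle the matter, because the sentence lists reporting to the IRB and compilation as two separate things, and on either reading the event content of the biostatistician's report is undefined. The layout of DSMB tables may well be left to another document. A stated rule on what is compiled that does not match the DSMB's remit is a different matter.

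Some stronger readings are tempting but not supported:

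- A reader might infer that the UC count must be near zero by definition. The filter refers to the study, not to RGT; UC gait training is a randomised arm with a set weekly amount, and Section 12 lists its risks for participants in general. Under-counting in UC is a probable consequence, not a certain one.
- A reader might infer that events are lost. They are not: all are identified, graded and evaluated by the principal investigator.
- A reader might infer that the filter can only hide harm from RGT. Under-counting UC events makes RGT look worse; only dropped RGT events work the other way.
- A reader might size the problem from the fracture incidence cited in Table 5. That figure describes fractures during exoskeleton use in a cited review and says nothing about how many events the filter removes.

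**Conclusion.** Wrong as written, as an internal contradiction: Sections 8 and 13 do not agree on which adverse events are compiled for review. The effect on the DSMB is conditional. It arises if the Section 13 compilation is what the biostatistician's report draws on, which the text leaves open. In that case the between-arm safety comparison depends on attribution by staff who know the arm, and it can err in either direction. The illustrated figures show that the distortion could be large, but they rest wholly on assumed event rates and attribution shares and on a test that the protocol does not specify.

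Severity is moderate. The primary outcome, its analysis and the sample size are untouched, and the underlying data exist.

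**What to change.** Reconcile the two sections.

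- In Section 13, limit the relatedness condition to IRB reporting, and name the body and the interval meant by the periodic review.
- In Section 8 or 13, add a sentence such as: *All adverse events and serious adverse events, regardless of attribution, are tabulated by randomised arm, with severity and attribution shown, in each DSMB report.*

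The cost is one or two sentences and one table per report. No new data collection is needed, because every event is already to be identified, graded and assigned a cause.
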